### Sample size

The purpose of this study is to detect the alpha diversity of gut microbiota in preterm infants (Shannon index is a better indicator of species richness and evenness) and group differences in short chain fatty acids of interest. At present, no study has reported the effect of OAC on the difference in alpha diversity of gut microbiota and metabolites between preterm infants receiving oropharyngeal administration of colostrum and those receiving sterile water. Therefore, it is difficult to estimate the expected change. However, clinically relevant differences in the Shannon index have been determined based on previous studies on the effect of different feeding types on the Shannon index of preterm infants at the 7th day of age [46–49]. According to these studies, the mean between-group difference in Shannon index ranged from 0.2 to 0.6 with a standard deviation of 0.2 to 0.8 and a mode of 0.6 [46–49]. In a study of the effect of OAC on oral microbiota, the mean between-group difference in Shannon index ranged from 0.2 to 0.5 [50]. Combined with these basic data, the mean difference in Shannon index is assumed to be 0.2, with a standard deviation of 0.6. We conducted sample size estimation using PASS 15.0 (NCSS, Kaysville, Utah, United States). To achieve a statistical power of 80% (2-sided type 1 error of 0.05), the calculated sample size of 143 patients for each group (286 in total) with a ratio of 1:1 will be used. In addition, the relevant difference in short chain fatty acids is based on the previous difference of acetic acid, the main metabolite of preterm infants at the 7th day of life with different feeding types. The mean value of the difference between groups of acetic acid is about 0.025 µmol/g, with a standard deviation of 0.02–0.1 for each group [51, 52]. Therefore, a sample of 92 infants in each group (184 in total) will provide 80% power to detect a difference in short chain fatty acids of at least 0.025, assuming a standard deviation of 0.06 and a 2-sided type I error of 0.05. In combination with these two sample sizes, we will use a relatively larger sample (143 cases). Assuming a loss of 10–12% to follow-up, we will need to include 160 infants in each group, resulting in a total sample size of 320. The sample size will be adjusted based on the results of interim analysis.

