## Outcomes

Primary outcome measures: 1a) a between-group difference in gut microbial alpha diversity will be measured using Shannon diversity index at the 7th day and 1b) a between-group difference in the concentration of fecal metabolites (short chain fatty acids) will be quantitatively measured using non-targeted liquid chromatography-mass spectrometry (LC–MS) at the 7th day.

Secondary outcome measures: 2a) between-group differences in other diversity indicators of gut microbiota, including Simpson index (an indicator of species richness and evenness less affected by rare species than Shannon index) and Chao1 index (estimated total number of species) at the 7th day; 2b) between-group differences in alpha diversity of gut microbiota measured using Shannon index, Simpson index and Chao1 index on the 14th, 21st and 28th days of life; 2c) Between-group differences in the concentration of fecal metabolites quantitatively measured by non-targeted LC–MS at the 14th, 21st and 28th days of life; 2d) proportion of gut microbiota at phylum and genus level; 2e) gut microbial beta diversity explaining between-sample dissimilarity calculated using the Vegan package; and 2f) correlation between the comparative dominant flora and metabolites (Table 1).

**Table 1 Tab1:** Outcomes, measures and methods of analysis

Outcome	Hypothesis	Outcome Measure	Methods of Analysis
**1.Primary** 1a A between-group difference in Shannon diversity index at the 7th day	OAC increases Shannon diversity and metabolites of gut microbiota	Shannon index (continuous)	Individuals: Wilcoxon text; Intergroup: T/Wilcoxon text
1b A between-group difference in fecal metabolites at the 7th day		Short chain fatty acids (continuous)	Individuals: FC, PCA/PLS-DA Intergroup: T/Wilcoxon text
2.** Secondary** 2a Between-group differences in other alpha diversity indexes (Simpson, Chao1) at the 7th day	OAC increases other alpha diversity and beta diversity, and changed the proportion of gut microbiota from birth to day 28. There is a Correlation between dominant microbiota and metabolites	Simpson index, Chao1 index (continuous)	Individuals: Wilcoxon text; Intergroup: T/Wilcoxon text
2b Between-group differences in Shannon index, Simpson index and Chao1 index at the 14th, 21st and 28th days of life		Shannon index, Simpson index, Chao1 index (continuous)	Individuals: Wilcoxon text; Intergroup: T/Wilcoxon text

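### Two primary endpoints are each sized and tested at an unadjusted 0.05, with no statement of whether either or both define success; the either-endpoint claim carries up to about 10% error

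*Protocol article*

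**What the plan says.** The Outcomes section lists two primary measures, both at day 7. The first is Shannon: "1a) a between-group difference in gut microbial alpha diversity will be measured using Shannon diversity index at the 7th day". The second, labelled 1b, compares the arms on fecal short chain fatty acid levels. Table 1 puts them under one hypothesis, "OAC increases Shannon diversity and metabolites of gut microbiota".

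The Sample size section treats them separately. For Shannon, "the mean difference in Shannon index is assumed to be 0.2, with a standard deviation of 0.6", and "To achieve a statistical power of 80% (2-sided type 1 error of 0.05), the calculated sample size of 143 patients for each group". For short chain fatty acids it relies on acetic acid (difference 0.025, SD 0.06) and reaches 92 per group, again at two-sided 0.05 and 80% power. The two are then merged by size alone: "In combination with these two sample sizes, we will use a relatively larger sample (143 cases"). Allowing for losses, 160 per group are to be enrolled.

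The Statistical analysis section sets one threshold, p < 0.05, for all tests. The article gives no success rule, testing order or division of alpha for the two primaries. The Quality control section adds an interim analysis of the primary endpoint, in the singular, at the 50% point. The Sample size section says the number of infants will be adjusted on its results.

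**The concern.** Taking the larger of two sample sizes gives each endpoint at least its planned power when that endpoint is considered alone. It does not settle what the trial as a whole may claim. If either endpoint is enough, two unadjusted tests at 0.05 give more than a 5% chance of a false primary claim. If both are needed, the chance of success is the chance of winning both, which cannot exceed the power for Shannon alone and will usually be lower.

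A second gap makes this worse. Endpoint 1b is a class of acids, while the calculation rests on acetic acid only, and the Sample size section speaks of acids of interest without listing them. The Background mentions both acetate and butyrate. The number of primary tests is therefore open, and the acid that carries the claim could be chosen after the results are seen.

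**Working it through.** **Inputs.** From Sample size: Shannon difference 0.2, SD 0.6; acetic acid difference 0.025, SD 0.06; two-sided 0.05; 80% power; 143 evaluable per arm. Allocation is 1:1. The correlation between the endpoints is not given, so I assume a range from 0 to 0.8.

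**1. Reproduce the plan's figures.** n per arm = 2 × (1.960 + 0.842)² × (SD/difference)².
- Shannon: 2 × 7.849 × 9 = 141.3, so 142; with the noncentral t, 143.
- Acetic acid: 2 × 7.849 × 5.76 = 90.4, so 91; with the noncentral t, 92.

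Both stated sizes reproduce.

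**2. Power for each endpoint at 143 per arm.** Expected test statistic = difference / (SD × √(2/143)).
- Shannon: 2.82, power 80.2% (t) or 80.5% (normal).
- Acetic acid: 3.52, power 94.0% (t) or 94.1% (normal).

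**3. Either endpoint suffices, each at 0.05.** Familywise error = 1 − P(|Z1| ≤ 1.96 and |Z2| ≤ 1.96).

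| Correlation | Familywise error |
|---|---|
| 0 | 1 − 0.95² = 9.75% |
| 0.5 | 9.1% |
| 0.8 | 7.8% |

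The bound under any dependence is 0.05 + 0.05 = 10%. Each further acid tested at 0.05 raises the error. As an illustration with independent tests, Shannon plus two acids gives 1 − 0.95³ = 14.3%, and Shannon plus three gives 1 − 0.95⁴ = 18.5%. The number of acids is my assumption, and acids of one class are unlikely to be independent.

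**4. Both endpoints required, each at 0.05.** Error stays at or below 5%. Joint power at 143 per arm:

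| Correlation | Joint power |
|---|---|
| 0 | 0.802 × 0.940 = 75.4% (t); 0.805 × 0.941 = 75.7% (normal) |
| 0.5 | 77.9% (normal) |
| 0.8 | 79.7% (normal) |

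Over every possible dependence the normal-approximation range is 74.6% to 80.5%.

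**5. Rules that hold 5% across the two tests at 143 per arm** (normal approximation; Holm by simulation, correlation 0 to 0.8).
- Holm: Shannon 79–80%, acetic acid 91–93%, at least one endpoint 91–97%.
- Fixed sequence, Shannon first at 0.05: Shannon 80%. Acetic acid is confirmatory only when both are significant, so its figure is the joint power in step 4, about 75–80%.
- Bonferroni at 0.025 each: Shannon 71–72%, acetic acid 90%, at least one endpoint 91–97%.

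**The case against.** The strongest reply is that the article claims 80% power and 5% error for each endpoint separately, and that both statements are arithmetically right. It nowhere promises 5% across the pair or 80% for the pair. A multiplicity procedure is also ordinary content for an analysis plan, which is not shown.

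The first part stands: the sample sizes are not miscalculated. The second stands only in part. The article is not merely silent, because it prints an unadjusted threshold for all tests and a specific way of combining two primaries. Followed as written, an either-endpoint claim exceeds 5%. A rule held elsewhere would still have to be reconciled with this text.

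Four stronger inferences are tempting, and the documents do not support them.
- **No reading can deliver both 5% error and 80% power.** A fixed sequence keeps 5% and 80% Shannon power at the planned size, and Holm comes within a point of it. With both endpoints required, the shortfall is about 0 to 5 points, depending on an unknown correlation.
- **The error is 18.5%.** That rests on three acids, a number the article does not give, and on independence among them.
- **The trial is too small because Bonferroni would need 173 per arm.** That figure restores 80% for Shannon alone. Under Bonferroni at 143 per arm, power for at least one endpoint is already 91–97%.
- **The word joining the two outcomes in Table 1 means both are required.** It forms part of a hypothesis and is not a decision rule.

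**Conclusion.** The point holds in this form: the article applies an unadjusted 0.05 to two primary endpoints and does not define success. An either-endpoint claim has about 7.8–9.75% error for correlations from 0.8 to 0, and more if several acids are tested. A both-endpoints claim keeps 5% error, but joint power is about 75–80% rather than a secure 80%.

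These figures rest on the plan's own differences and SDs, on 143 evaluable infants per arm, and on an assumed correlation range. They exclude any inflation from the interim analysis. The defect matters because the missing rule decides whether the trial is positive, but it can be closed without changing the sample size.

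**What to change.** Name day-7 acetic acid, the acid that was sized, as the single measure for endpoint 1b, and make all other acids secondary. Then state one of the following in Outcomes and Sample size.
- **Holm across Shannon and acetic acid at overall two-sided 0.05.** Power at 143 per arm is 79–80% for Shannon and 91–93% for acetic acid.
- **Fixed sequence:** Shannon at 0.05, then acetic acid at 0.05 only if Shannon is significant. Shannon keeps 80%; acetic acid is confirmatory in about 75–80%.
- **Both required:** each at 0.05, with the stated power changed to about 75–80% and the assumed correlation given.

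No extra infants are needed. The cost is slightly lower confirmatory power for one endpoint: small under Holm, larger for acetic acid under the fixed sequence. The Trial status section says recruitment is under way, so this is a protocol amendment. It should be in place before the interim look, where the monitoring committee has unblinded access to the data.

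This change does not cover the interim analysis itself. That look, and the sample-size adjustment tied to it, need their own error control and a statement of which primary endpoint is examined.

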### Statistical analysis

Intention to treat (ITT) method will be used for statistical analysis. Baseline maternal and infant demographic and clinical characteristics of OAC group and placebo group will be compared using chi-square or Fisher’s exact test (such as infant sex, mode of delivery and presence or absence of chorioamnionitis) and t-test or Wilcoxon test for continuous variables. After removing low-quality sequences, original data will be analyzed following the steps of 16S rRNA discovery, clustering and identification. The number of operational taxonomic units (OTUs) will be calculated for each sample at a 97% sequence similarity level. A specific taxonomic unit will represent a specific species. Subsequently, a sparse curve will be drawn based on the results of OTUs generated using sample sequencing. Wilcoxon test will be used to analyze the diversity and richness of microbiota within individuals. A t-test or Wilcoxon test will be used to compare alpha diversity (Shannon index, Simpson index, and Chao1 index) between the two groups of infants with and without OAC intervention within four weeks of birth. Repeated measures analysis of variance (ANOVA) (for normally distributed data) or Kruskal Wallis test (for non-normal data) will be used to evaluate the microbial alpha diversity at different time points. The proportion difference of gut microbiota at the phylum and genus levels will be calculated using chi-square or Fisher's exact test. Values with *p* < 0.05 will be considered statistically significant. Beta diversity will be calculated using the Vegan package, and a principal co-ordinates analysis (PCOA) based on Bray–Curtis distances will be plotted. Adonis permutational multivariate analysis of variance of Bray–Curtis distances with 9999 permutations will be used to compare microbial community structure between each of the two groups.

Redundancy analysis (RDA) will be performed using the Vegan package to define the factors that could significantly affect gut microbial composition in each group. We will use Linear discriminant analysis (LDA) of effect size (LEfSe) to determine the most discriminant taxa between the two groups. If the effect of OAC intervention on gut microbiota is less than that of other confounding factors (delivery mode, antibiotic use, feeding type, etc.), we will adjust it with RDA.

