**Fig. 2 Fig2:**
[figure not shown]
Quality control process of the protocol. DMC, data monitoring committee (composed of data verifiers at the coordination center and the principal investigators at each center); CRF, case report form. * The research team of each center is composed of the principal investigator, data quality controller, syringe preparing nurse and the intervener. ** The trial steering committee (composed of the directors of neonatal pediatrics at each center and the heads of the medical safety review team)

The whole research team will hold online meetings every month through multimedia video conferencing software to discuss the implementation of the scheme as needed and quickly solve any problems. When 50% of randomly assigned patients completed five stool samples collection, the primary endpoint was analyzed in the interim. An interim-analysis will be conducted by independent statisticians without knowledge of treatment allocation. Statisticians will report to the DMC. The DMC will conduct non-blind access to all data and discuss the results of the interim analysis, adverse events and compliance with the trial steering committee (composed of the directors of neonatal pediatrics at each center and the heads of the medical safety review team) at the multicenter meeting. Adverse events are defined as aspiration to the lungs, resuscitation due to severe bradycardia or apnea after intervention, and postnatal infection with cytomegalovirus thought to be associated with fresh breast milk. If cases related to these adverse events occur, we will intervene immediately. To ensure the safety of the included infants, vital signs will be carefully monitored during oropharyngeal administration. If the vital signs are unstable, the intervention will be stopped in time. The trial steering committee will decide to continue the trial and report to the ethics committee, which is independent of the sponsor and investigators (Fig. 2).

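### The sample size is to be changed on an interim analysis of the between-group primary endpoint while the final test stays at an unadjusted 0.05, so the 5% type I error is not protected, and the article contradicts itself on who is unblinded

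*Protocol article*

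**What the plan says.** - **Interim look** (Quality control, text after Fig. 2): "When 50% of randomly assigned patients completed five stool samples collection, the primary endpoint was analyzed in the interim". The Outcomes section defines both primary outcomes, Shannon index and short chain fatty acids, as between-group differences at day 7.
- **Consequence of the look** (Sample size): "The sample size will be adjusted based on the results of interim analysis". No rule, limit or cap is given.
- **Significance level** (Statistical analysis): p-values below 0.05 "will be considered statistically significant". The design uses the same level: "To achieve a statistical power of 80% (2-sided type 1 error of 0.05").
- **Who sees what** (Quality control): "An interim-analysis will be conducted by independent statisticians without knowledge of treatment allocation". These statisticians report to the DMC, which has unblinded access to all data and discusses the interim results with the trial steering committee. Earlier in the same section the DMC is made up of the data verifiers and the principal investigators of the centres. The Randomization section lists the principal investigator and the data verifier among those who are blinded.

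**The concern.** A final test at 0.05 has a 5% error rate if the number of infants is fixed, or changes only for reasons unrelated to the observed treatment difference. Here the interim analyses the treatment comparison itself, and the sample size then follows from its results. If the size responds to the observed difference, the usual final statistic no longer has its nominal distribution. The reported p-value and confidence interval can then be too favourable.

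A second problem is who holds the results. If centre investigators and data verifiers see unblinded interim results while infants are still being recruited, the double-blind claim is weakened where recruitment and data checking take place. Neither problem can be repaired after an unblinded look has driven the sample size.

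**Working it through.** **1. The plan's own figures.** Inputs from Sample size: "the mean difference in Shannon index is assumed to be 0.2, with a standard deviation of 0.6"; "a difference in short chain fatty acids of at least 0.025, assuming a standard deviation of 0.06"; two-sided 0.05; 80% power. Formula: n per group = 2·SD²·(1.96 + 0.84)²/difference², with (1.96 + 0.84)² ≈ 7.85.
- Shannon: 2 × 0.36 × 7.85/0.04 = 141.3, so 142. The t-test version gives 142.2, so 143, as stated.
- Short chain fatty acids: 2 × 0.0036 × 7.85/0.000625 = 90.4, so 91. The t-test version gives 91.4, so 92, as stated.
- Loss: 143/0.90 = 159 and 143/0.88 = 163 after rounding up, so 160 per group is in line.

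The arithmetic is right. It is that of a single-look design spending the full 0.05 at the end, with no allowance for the interim.

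**2. Model for the resizing.** Let z1 be the interim statistic at half the planned information, and let the second stage be r times the first (planned r = 1). The unadjusted final statistic is Z = (z1 + √r·Z2)/√(1 + r), significant if |Z| > 1.96. With no true effect, the chance of a significant final result given z1 is

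1 − Φ[(1.96√(1+r) − z1)/√r] + Φ[(−1.96√(1+r) − z1)/√r].

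Examples: at z1 = 0.5 it rises from 1.2% (r = 1) to 3.0% (r = 3). At z1 = 1.5 it falls from 10.2% to 8.2%. Enlarging the trial after a weak result therefore adds false positives, and enlarging it after a strong result does not. Type I error is the average of this chance over the null distribution of z1.

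**3. Results, final test left at 0.05.** The article states no rule, so every rule below is an assumption. Caps of 2, 3 and 5 times the planned second stage equal 1.5, 2 and 3 times the planned total.

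| Assumed rule | Type I error |
|---|---|
| Size fixed, no interim claim | 5.0% |
| Blinded pooled-SD re-estimation (200,000 simulated trials) | 4.98% |
| Increase only if conditional power is at least 50%, total capped at 2 times plan | 4.8% |
| Increase to 80% conditional power on the observed effect, caps 2, 3, 5 | 5.7%, 6.1%, 6.5% |
| Increase to the total giving 80% power at the observed effect, same caps | 5.6%, 6.0%, 6.4% |
| As the previous row, but size may also fall as far as the interim number | 6.4%, 6.8%, 7.2% |
| No resizing, but success claimable at p<0.05 at either look | 8.3% |

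**4. Levels that would keep 5% with a look at half the information and a fixed second stage.** The pair 0.0052 and 0.0480 (classical O'Brien-Fleming) totals 5.00%. So does about 0.003 and 0.049 (the O'Brien-Fleming-type spending function). Mixing the two families, 0.005 and 0.049, totals 5.09%.

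**5. Cost of staying blinded.** If the true difference is the planned 0.2, the pooled variance is raised by 0.2²/4 = 0.01, from 0.36 to 0.37. The SD then reads 0.608 instead of 0.600, and the required number rises by 0.37/0.36, from 143 to about 147 per group.

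**6. Roles side by side.**
- Randomization: principal investigator and data verifier blinded.
- Quality control, composition: the DMC is the data verifiers plus the centre principal investigators.
- Quality control, interim: the statisticians are blinded, and the DMC that receives their report is unblinded.

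These statements cannot all be followed.

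**The case against.** The strongest defence is that the interim statisticians work without the allocation. If they use pooled data only, resizing on the variance leaves the error rate at 5%. A rule that enlarges the trial only when results are promising would also be safe. Stopping boundaries and re-estimation rules are commonly left to a full protocol or SAP, and their absence from an article is no fault in itself.

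Part of this stands: the text does not show that 5% fails, only that nothing secures it. The defence does not remove the point. The analysed quantity is a between-group difference, the DMC is unblinded, resizing is tied to the results, and nothing limits it to a blinded variance.

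A reader might infer more, which the article does not support:
- **That type I error is 8.3%.** This needs a success claim at p<0.05 at the interim. No section provides for one. The steering committee's decision on continuing follows the sentences on adverse events and vital signs and can be read as a safety decision.
- **That it is about 16%.** This is 1 − (1 − 0.083)² for two independent primary outcomes, each tested at two looks. With a single look the same reasoning already gives 1 − 0.95² = 9.75%, so most of it comes from having two primaries, a separate question. Independence is also assumed.
- **That the five-stool trigger makes the look too late to be useful.** With the article's 10–12% loss, 160 completers need 160/0.90 to 160/0.88, about 178 to 182 randomised. Some 25 more enter during a 28-day wait (320 × 28/365), giving about 205 of 320. If each stool were independently missed 10% of the time (an assumption), 0.9⁵ = 0.59 and 160/0.59 = 271, still below 320. Waiting for day 28 gains nothing for day-7 outcomes, but it does not prevent resizing.

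**Conclusion.** The point holds in this form: as written, the article combines effect-capable resizing with an unadjusted final 0.05, so the stated 5% is not protected. Resizing is the feature actually stated. Under assumed rules that increase the size on the observed effect, with no early claim, type I error is about 5.5% to 6.5%, and somewhat higher (6.4% to 7.2% under one rule) if the size may also fall. These figures assume one look at half the planned information and second-stage caps of 2 to 5 times plan. A blinded variance-only review would leave 5%. The inflation is modest, but it falls on the primary comparison and cannot be undone afterwards.

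The contradiction over who is blinded rests on no assumed rule. It follows from the Randomization and Quality control sections alone.

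**What to change.** - **Recommended wording for Sample size and Quality control.** State that the interim is a blinded sample-size review. It re-estimates only the pooled SD (both arms together) of day-7 Shannon, the outcome that sets the sample size, with no between-arm comparison and no effect-based resizing. The final 0.05 then stands. The review can be triggered on day-7 stools, since both primary outcomes are measured on day 7.
- **If an efficacy look is wanted.** Use a consistent pair of levels: 0.0052 at the interim and 0.0480 at the end, or about 0.003 and 0.049 with the spending function. If the size may respond to the observed effect, also use a pre-weighted inverse-normal combination test at the final analysis.
- **Roles.** Reconcile Randomization with both parts of Quality control, so that they agree on who may see unblinded data and those described as blinded do not.

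Cost: wording in a few paragraphs and no extra infants at the outset, although a larger SD than planned could raise the number later. Under the blinded review, no early efficacy claim or effect-driven resizing is possible.
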